## Abstract

**Introduction:**

Raised blood pressure (BP) is common after stroke and is associated with a poor prognosis, yet trials of BP lowering in the immediate poststroke period have not demonstrated a benefit. One possible explanation for this may be that BP variability (BPV) rather than absolute levels predicts outcome, as BPV is increased after stroke and is associated with poor outcomes. Furthermore, there is evidence of distinct antihypertensive class effects on BPV despite similar BP-lowering effects. However, whether BPV in the immediate poststroke period is a therapeutic target has not been prospectively investigated.

The objectives of this trial are to assess the feasibility and safety of recruiting patients following an acute ischaemic stroke or transient ischaemic attack (TIA) to an interventional randomised controlled trial comparing the effects of two different antihypertensive drug classes on BPV. Secondary exploratory objectives are to assess if different therapeutic strategies have diverse effects on levels of BPV and if this has an impact on outcomes.

**Methods:**

150 adult patients with first-ever ischaemic stroke or TIA who require antihypertensive therapy for secondary prevention will be recruited within 7 days of the event from stroke services across three sites. After baseline assessments they will be randomly assigned to treatment with a calcium channel blocker or ACE inhibitor/angiotensin receptor blocker-based regimen and followed up for a period of three months.

**Ethics and dissemination:**

Ethical and regulatory approvals have been granted. Dissemination is planned via publication in peer-reviewed medical journals and presentation at relevant conferences.

**Trial registration number:**

ISRCTN10853487.

Strengths and limitations of this studyTo our knowledge, this is the first prospective randomised trial designed to assess the treatment of blood pressure variability (BPV) following acute ischaemic stroke/transient ischaemic attack.The protocol incorporates multiple blood pressure measurement methods.The chosen therapeutic interventions are in line with standard clinical practice for secondary stroke prevention.The trial is open label which could bias the analysis of treatment effects on BPV and any impact on stroke outcomes, but these are secondary exploratory outcomes in this feasibility trial.

## Introduction

### Background

Raised blood pressure (BP) is common after acute stroke with at least 75% of patients having a systolic BP (SBP) >130 mm Hg at hospital admission^1 2^; SBP <130 mm Hg being the guideline target for secondary prevention following stroke.^3^ Increased poststroke BP is associated with poor prognosis^4 5^ and may result from raised intracranial pressure,^6^ increased sympathetic nervous system activity,^7^ abnormal baroreceptor sensitivity (BRS),^8^ haematoma expansion,^9^ cerebral oedema^10^ and a white-coat response.^11^ A spontaneous BP decrease usually occurs 4–10 days after ictus,^12^ but substantial BP reductions can be associated with cerebral hypoperfusion as a consequence of poststroke dysautoregulation.^13^ We have previously reported that both increased 24 hours and beat-to-beat BP levels following acute stroke are associated with a poor prognosis.^14–16^ Subsequently, data from the International Stroke Trial have suggested a U-shaped relation between baseline SBP (within 48 hours of stroke) and short-term (14-day mortality) and long-term (6-month death and dependency) outcomes; the lowest risk of death and dependency being at SBP 150 mm Hg.^17^ However, there is conflicting evidence regarding acute stroke hypertension treatment. Data from randomised controlled trials (RCT) suggest that BP can be safely reduced after the acute stroke period, however, there seems to be no indication that doing so is beneficial.^18–23^ Indeed, the Scandinavian Candesartan Acute Stroke Trial reported that it may actually be harmful, with a non-significant increased risk of poor 6-month functional outcome.^23^ Therefore, Cochrane meta-analysis and guidelines state that optimal BP management in the context of initial stroke management remains uncertain.^3 24–26^

An alternative explanation for the lack of evidence that lowering elevated BP levels in acute stroke is beneficial may relate to the additional effects of BP variability (BPV).^27^ Current hypertension guidelines predominantly focus on mean, usually casual, BP measurements, dismissing BPV as random and merely an obstacle to the reliable estimation of usual BP. However, on ambulatory or home BP monitoring, which are recommended for the diagnosis and management of hypertension,^28^ mean BP is found to vary substantially,^29^ with the extent of this variation associated with visit-to-visit variability in clinic BP.^30^ Indeed, there are many examples to support the potential importance of BPV for vascular risk.^30^ First, the predictive value of estimated usual SBP and stroke risk falls with age,^31^ yet stroke incidence rises with age and the relative benefit of antihypertensive therapy is maintained in the elderly.^32^ Second, an increased early-morning surge in BP is predictive of stroke, but is poorly associated with mean BP.^33^ Third, other causes of transient hypertension are recognised triggers of vascular events, including sympathetic overactivity and orthostatic hypertension.^34^ Fourth, in the majority of studies, there is no threshold of baseline SBP below which vascular risk stops falling (though evidence for BP below 115/75 mm Hg is very limited),^31^ with antihypertensive therapy reducing risk even at ‘normal’ baseline SBP.^35^ Fifth, ‘white-coat’ hypertension, a common example of situational BPV, is associated with long-term target organ damage independent of mean BP.^36^ Sixth, though hypertension is a recognised risk factor for vascular dementia, there is limited evidence of reduced dementia risk in trials of antihypertensive therapy. However, a trial of calcium channel blockers (CCB), which have the most consistent effect on reducing BPV,^37 38^ has shown a substantial reduction in the incidence of dementia.^39^ Furthermore, in patients with Alzheimer’s dementia BPV is increased compared with matched controls, with increased BPV being independently predictive of progressive cognitive decline in this patient group.^40^ Finally, specific group differences in stroke risk are not accounted for by mean BP alone, for example, in black individuals.^41^

### Rationale for the study

In a retrospective analysis of RCTs in a transient ischaemic attack (TIA) population, visit-to-visit intraindividual BPV was a risk factor for stroke independent of the mean ‘absolute’ BP level, and perhaps of greater significance.^30^ Additionally, within-visit systolic BPV, based on casual BP measurements, was correlated with visit-to-visit systolic BPV, but was a weak predictor of future vascular events.^30^ Importantly, in a separate analysis it was demonstrated that BPV is reproducible and independent of confounding factors.^42^ Increased BPV may also be an important predictor of short-term outcome following acute stroke. Robinson and colleagues have shown that beat-to-beat systolic BPV was greater in acute stroke compared with controls,^43^ and that high mean arterial and diastolic beat-to-beat BPV was associated with a worse prognosis.^15^ Furthermore, in a post hoc analysis of the Tinzaparin in Acute Ischaemic Stroke Trial, high systolic BPV from three to six casual BP readings, taken within 48 hours of symptom onset, was associated with an increase in death or early neurological deterioration at day 10.^44^ Conversely, a retrospective analysis of nearly 1000 patients in the Continue or Stop Post-Stroke Antihypertensives Collaborative Study and Controlling Hypertension and Hypotension Immediately Post Stroke trial did not demonstrate a significant association between systolic BPV based on two sets of three casual BP readings within 48 hours of stroke onset and 2-week death and dependency.^45^ Overall, a recent meta-analysis reported that increased systolic BPV, measured early from stroke onset, was associated with poor long-term functional outcome.^46^ Furthermore, increased BPV may also relate to poststroke cognitive outcomes with evidence suggesting an association with signs of cerebrovascular small vessel disease on neuroimaging,^47^ and deterioration in cognitive test scores.^48 49^

Clearly, there is further scope to explore the relationship between BPV and outcome following acute stroke, in particular whether it has implications for therapeutic management in the immediate poststroke period. Rothwell’s group have explored the differential effects of BP-lowering therapies on BPV in a hypertensive population.^37 38^ Though clinical benefits with reduction in risk of stroke and coronary events were seen for all classes of antihypertensive agent, class-specific effects existed; CCBs reduce stroke risk to a greater extent than expected from mean SBP reduction alone, and beta-blockers (BB) to a smaller extent. A detailed analysis of the Anglo-Scandinavian Cardiac Outcomes Trial-Blood Pressure Lowering Arm, comparing an amlodipine versus atenolol-based regime, and the Medical Research Council trial, comparing an atenolol versus diuretic-based regime, reported opposite effects of CCB and BB on systolic BPV. In addition, this differential effect accounted for the disparity in observed effects on stroke risk and observed effects on mean SBP.^38^ This was confirmed in a systematic review and meta-analysis of 389 RCTs which also demonstrated that BPV is reduced by non-loop diuretic drugs, but increased by ACE inhibitors (ACEI) and angiotensin receptor blockers (ARB).^37^ Again, the effects on systolic BPV were correlated with effects on stroke risk independent of differences in mean SBP.^37^ Prospective trials to investigate these apparent medication class effects on BPV would be valuable, especially comparing CCB and ACEI/ARB which are typically the first-line antihypertensive drug classes. If, as anticipated, CCBs reduce BPV whereas ACEI and ARBs increase it this could be relevant after acute stroke, where normal cardiovascular autonomic and cerebrovascular autoregulatory pathways are impaired. BRS is important in the short-term regulation of the cardiovascular system, including BP, and is known to be impaired following acute ischaemic stroke,^8^ and associated with poor short-term and long-term prognosis.^50^ In addition, it is well established that cerebral autoregulation (CA) is impaired, particularly following moderate to severe stroke.^13^ As a consequence, cerebral perfusion is pressure dependent, and therefore hypertensive episodes related to increased BPV may contribute to reperfusion injuries, for example, postischaemic oedema and/or intracerebral haemorrhage. Conversely, hypotensive episodes associated with increased BPV in the presence of impaired CA may lead to secondary ischaemia, particularly in the absence of a good collateral circulation.

In conclusion, increased BPV is associated with a greater vascular risk, independent of mean BP and may predict poor outcomes after stroke. Furthermore, commonly used antihypertensive agents have different class effects on BPV which may in part explain the overall differential effects on stroke risk for similar absolute reductions in mean BP in a hypertensive population. Trials to investigate the potential therapeutic targeting of BPV and any potential benefit of doing so in acute stroke would be useful to address gaps in the current knowledge base.

### Study objectives

The primary objective of this study is to determine the feasibility of recruiting patients with acute stroke and TIA into an interventional randomised trial comparing the effect of different antihypertensive medication regimens on BPV.

Secondary feasibility objectives are:To determine the viability of measuring changes in BPV from baseline to 21 (±7) days and 90 (±14) days by treatment arm.To assess compliance rates with BPV measurement methods.To assess compliance rates with the investigational treatments.To identify serious adverse events (SAE) associated with the interventions, including recurrent stroke/TIA, other cardiovascular events, death and hospital readmission up to 3 months.

In addition to the feasibility objectives, exploratory outcomes that may be used in a future definitive RCT will be investigated. The proposed primary exploratory outcome will be modified Rankin Scale (mRS) score at day 90.

Exploratory secondary outcomes are:mRS at day 21.National Institutes of Health Stroke Scale (NIHSS) at day 21.Mean BP at day 21 and day 90.BPV at day 21 day and 90.Montreal Cognitive Assessment (MoCA) score at day 90.

## Methods and analysis

### Study overview

This study is a randomised, multicentre, open-label parallel group study to determine the feasibility of conducting such a trial in a National Health Service (NHS) setting to investigate class effects of antihypertensive medications on BPV in patients with acute ischaemic stroke or TIA. The aim is to evaluate barriers to recruitment, identify potential safety issues and demonstrate that it is possible to detect differences in BPV over the proposed study duration. We also hope to investigate the potential therapeutic benefit of targeting BPV after acute ischaemic stroke/TIA in terms of functional outcome in order to help estimate the necessary sample size for a future definitive trial. A summary of the study design is provided in figure 1. Recruitment commenced in January 2018 and is ongoing. The trial was prospectively registered: International Standard Randomised Controlled Trial Number 10853487.

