### Randomisation

After the baseline assessments eligible patients will be randomised using a computer-generated protocol, in blocks of 4, to a dihydropyridine CCB or ACEI/ARB-based regime. The study treatment will be dispensed at the baseline visit, but treatment will not be commenced within 48 hours of the qualifying event in keeping with current recommended practice. The actual therapeutic agent used will be at the discretion of the treating clinician, but dictated by the class of therapy that the participant is assigned to. Prescription of the medication will be done by the treating clinician and the initial supply will be dispensed by the treating hospital or community pharmacy in accordance with the hospital’s policy for providing discharge or outpatient medication. Further supplies will be provided by the participant’s GP. Unblinding will not be necessary as there is an open-label study design.

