#### BP measurements

Baseline casual BP will be calculated as a mean of two sets of three supine brachial BP readings taken 10 min apart using a UA767 BP monitor (referred to as enhanced casual BP).

Three consecutive periods of 10 min beat-to-beat non-invasive BP monitoring in the supine position using the middle finger of the non-hemiparetic hand will be recorded with a Finometer device. The servo adjust mechanism of the Finometer will be switched off during the recording period, but applied at 10 min intervals during the monitoring period.

Daytime ambulatory BP monitoring (ABPM) will be performed using a SpaceLabs 90207 monitor, programmed to measure BP at 20 min intervals. Daytime is defined as between 07:00 and 22:00 hours.

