### Sample size calculation

A feasibility study of 150 patients (64 patients per group with a 15% dropout rate) will have an 80% power at the 5% significance level of detecting an 8 mm Hg difference in systolic BPV between the CCB and ACEI/ARB-based regimes, assuming a mean systolic BPV SD of 14.97 mm Hg in the CCB arm and 16.95 mm Hg in the ACEI/ARB arm.^37^

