#### Assessment of the intervention

Compliance with the intervention will be assessed by the proportion of participants who achieve ≥80% adherence to the trial medication and the proportion of participants who have all BP measurements recorded successfully.

The feasibility of detecting changes in BPV will also be assessed. Within-individual systolic, diastolic and mean BPV will be expressed as the SD, coefficient of variation, average real variability and variation independent of the mean calculated from all BP measurements: enhanced casual, beat-to-beat measurements (each 10 min recording and the total 30 min recording), and daytime ABPM.^42^ Changes in within-individual BPV from baseline to the follow-up time points will be analysed using a general linear model. The size of the mean difference will be estimated for each approach and compared to select the most appropriate measure for a future study.

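### The measure of blood pressure variability for a future trial is chosen by the raw size of the mean difference, which depends on drug effect, chance and units and takes no account of how noisily each method measures

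*Protocol article*

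**What the plan says.** The Study overview lists among the trial's aims to "demonstrate that it is possible to detect differences in BPV over the proposed study duration". The first secondary feasibility objective (Study objectives) is "To determine the viability of measuring changes in BPV from baseline to 21 (±7) days and 90 (±14) days by treatment arm".

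The evidence for this is set out in three places:

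- **Secondary feasibility outcome measures:** BPV change by arm, and completion and failure rates of the BPV measurements.
- **Assessment of the intervention:** the proportion of patients with every BP measurement recorded. Then, "The feasibility of detecting changes in BPV will also be assessed": systolic, diastolic and mean BPV are each expressed by four indices (SD, coefficient of variation, average real variability, variation independent of the mean). These are computed from the casual readings, each 10 min beat-to-beat recording, the 30 min total, and daytime ambulatory monitoring (ABPM). A general linear model is fitted to change from baseline. The mean difference under each approach is then estimated, and its size is the stated basis for choosing the future measure.
- **Exploratory analyses:** a general linear model for the arm effect on each expression of BPV.

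The BP measurements section already provides replicates: "Three consecutive periods of 10 min beat-to-beat non-invasive BP monitoring in the supine position", and two sets of three casual readings 10 min apart. ABPM is one recording per visit, at baseline and day 90 only (Table 1). The rationale cites an external analysis finding BPV reproducible. It gives no figure and does not tie the finding to these three methods soon after stroke.

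**The concern.** Whether a method can measure BPV change and whether two drug classes change BPV differently are separate questions. The stated rule answers the first with a quantity governed largely by the second. If the mean difference is read as change from baseline, it also carries recovery; the Background notes a spontaneous BP fall 4–10 days after onset.

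Three further faults lie in the rule itself. It picks among many correlated candidates. It sets mm Hg against ratios. It gives no credit to a method for being precise.

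At stake is the choice of BPV measure for the next trial. Followed as written, the rule could carry forward a noisy method that happened to show a large difference, or drop a precise one that did not.

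**Working it through.** **1. The plan's own figure.** Inputs from Sample size calculation: "A feasibility study of 150 patients (64 patients per group with a 15% dropout rate"), 80% power, 5% significance, 8 mm Hg, and SDs of 14.97 and 16.95 mm Hg.
- Pooled SD = √[(14.97² + 16.95²)/2] = 15.99.
- Patients per arm = 2(1.96 + 0.842)² × 15.99²/8² = 62.7, so 63 by the normal formula. The t-test version gives 63.7, so 64.
- 128/0.85 = 150.6.

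The stated size reproduces with a two-sided test, so the point is not an arithmetic one. The calculation uses one pair of SDs and does not say which device or index they describe.

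**2. How many candidates.** 3 pressures × 4 indices × 6 recordings (casual, three 10 min, one 30 min, ABPM) = 72 at day 90. Without ABPM, 3 × 4 × 5 = 60 at day 21. They are strongly correlated, so I put no figure on the selection bias.

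**3. Units.** Assume, for illustration, a mean systolic BP of 130 mm Hg in both arms. A difference of 8 mm Hg in SD is then a difference of 8/130 = 0.062 in coefficient of variation. It is the same effect in the same patients, yet the raw sizes cannot be ranked.

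**4. Noise by method.** Inputs from BP measurements: casual n = 2 × 3 = 6. ABPM every 20 min over 07:00–22:00 gives about 15 × 3 = 45. For independent normal readings the sampling coefficient of variation (cv) of an SD is √(1 − c4²)/c4, where c4 is the usual small-sample factor for an SD:

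| Readings | c4 | cv |
|---|---|---|
| 3 (one casual set) | 0.886 | 52% |
| 6 (both casual sets) | 0.952 | 32% |
| 45 (ABPM) | 0.994 | 11% |

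Let t be the true between-patient coefficient of variation of BPV, assumed 0.2 to 0.4. Reliability = t²/[t² + cv²(1 + t²)].
- Casual: 0.04/(0.04 + 0.1045 × 1.04) = 0.27 at t = 0.2, and 0.57 at t = 0.4.
- ABPM: 0.77 and 0.92.
- Ratios: 2.9 and 1.6. These are the relative numbers of patients needed if both methods carried the same true effect.

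**5. What that does to the rule.** At equal average BPV, the casual difference has a standard error √2.9 = 1.7 to √1.6 = 1.3 times that of ABPM. If the arms truly do not differ and the two errors are independent, casual shows the larger absolute difference with probability (2/π)·arctan(ratio) = 0.66 to 0.58, where equal noise would give 0.50. The raw rule therefore leans towards the noisier method.

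**6. What the planned models can show.** The 95% CI half-width at 64 per arm is about 1.98 × 15.99 × √(2/64) = 5.6 mm Hg. A simulation holding total SD at 15.99 gave 5.58 at reliability 0.95 and 5.58 at 0.40. Total noise is visible; its split is not.

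**7. What the replicates could give.** Three recordings in 150 patients, intraclass correlation (ICC) 0.7: F = (1 + 2 × 0.7)/0.3 = 8. Limits are 8/1.313 = 6.09 and 8 × 1.330 = 10.64. With ICC = (F − 1)/(F + 2), the 95% CI is 0.63 to 0.76.

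**The case against.** The strongest reply is that repeatability models usually belong in an analysis plan, that this is a condensed article, and that BPV will in any case be computed for each 10 min recording. That stands for the missing ICC taken alone. It does not cover the selection rule, which the article states.

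A reader might go further and infer that a null result could not be told from a noisy measure. The document does not support that. The general linear models yield a residual SD and a confidence interval, so a precise null differs visibly from an imprecise one. What they leave unresolved is the source of the noise.

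A reader might also infer that the definitive trial would lack the figure driving its size. That fails too. A parallel-group sample size rests on the total observed SD, which this trial will supply, and the proposed primary outcome for a future trial is the modified Rankin Scale at day 90. Nor does the article say that a null arm difference would mean BPV change is unmeasurable. Completion rates are judged separately, and the arm effect on BPV is already labelled exploratory.

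Objections to the remedy also stand in part:
- The replicates lie within one session and omit day-to-day variation.
- ABPM has no true replicate within a visit, and odd/even splitting changes the spacing from 20 to 40 min, which alters average real variability.
- A repeatable measure need not be sensitive to treatment.
- A short supine series and a daytime recording may not measure the same quantity, so the 1.6- to 2.9-fold ratio is illustrative.

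**Conclusion.** The point holds as a criticism of the stated selection rule. Raw mean difference mixes drug effect and chance with measurement quality, is not comparable across indices, and ignores noise that plausibly differs about threefold between casual and ambulatory SDs (32% against 11%). Those two figures assume independent normal readings. The reliabilities (0.27–0.57 against 0.77–0.92) also rest on an assumed between-patient coefficient of variation of 20–40%, and neither set covers the beat-to-beat recordings.

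The change should be made because a stated feasibility objective and the choice of a future BPV measure depend on it. It does not touch recruitment and retention, the primary feasibility outcome, or the stated sample size.

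**What to change.** In the assessment of the intervention, replace selection by raw mean difference with selection on three criteria:

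1. The rate of usable recordings.
2. Within-session repeatability: ICC and within-patient SD, each with a 95% CI, from a patient random-effects model. Use the three 10 min beat-to-beat recordings and the two casual sets, noting that the casual estimate describes a 3-reading SD (sampling cv about 52%), not the 6-reading one.
3. The standardised difference or change (estimate divided by its SD), with its CI.

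For ABPM, report a split-recording estimate for SD and coefficient of variation only, labelled approximate.

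State there, and in the Study objectives and Study overview, that viability of measuring BPV change is judged whether or not the arms differ. Add that within-session repeatability omits day-to-day variation, so any smallest detectable change derived from it is a lower bound.

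The cost is a few extra variance-component models on data already collected, with no new patients or measurements. Some methods may look less favourable than under the present rule.
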